**Fig 1 pone.0346723.g001:**
[figure not shown]
Schedule of the trial.

This study will be carried out in Beijing Anzhen Hospital and 6 subcenters (Fuwai Hospital, Chinese Academy of Medical Sciences, Beijing Tongren Hospital, Beijing Hospital, Beijing Chaoyang Hospital, Xuanwu Hospital) in China. From June 2022, consecutive post-stent patients with available CCTA data were prospectively enrolled. Invasive FFR will be performed according to clinical and imaging indications within 3 months of CCTA. For the purposes of supplementary training and diagnostic performance analysis, only patients with available invasive FFR measurements will be included. Patients without invasive FFR data will be excluded. Among them, 250 patients from Beijing Anzhen Hospital will be used to adapt and extend the existing DEEPVESSEL model [18], a deep learning–based CT-FFR computational software designed for the non-invasive functional assessment of coronary artery disease and previously validated in de novo coronary lesions, for application in the assessment of in-stent restenosis (ISR), and 81 patients from the other 6 subcenters will be used in external validation (Fig 2).

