### Study process

Prospective patients enrollment for this study began in June 2022 and is currently ongoing. Data collection (including demographic information, imaging data, laboratory tests, and interventional procedure parameters) and data analysis are scheduled to be finalized in 2026.

During the data collection process, all information will undergo rigorous de-identification to ensure that researchers will not have access to any personally identifiable information of participants at any stage.

Patients will be prospectively enrolled into the study, and their CCTA and invasive FFR data will be systematically collected according to this protocol. All data, including demographic characteristics, medical history, laboratory results, and clinical examinations (ECG, ICA, CCTA, and echocardiography), will be systematically recorded and stored using an electronic data capture (EDC) system.

All CCTA examinations will be acquired using multidetector CT scanners with ≥64 detector rows, in strict adherence to the 2022 Society of Cardiovascular Computed Tomography(SCCT) guidelines. When the CCTA image quality is suboptimal (e.g., obvious motion artifacts or blooming artifacts) or couldn’t satisfy the subsequent CT-FFR analysis, the patient will be censored out. Because this study is still ongoing and patient enrollment has not yet been completed, patients excluded due to poor image quality will be replaced by continued recruitment until the predefined sample size is reached.

FFR will be performed in intermediate stenosis (30–90% stenosis in vessel diameter) with a vessel size of at least 2 mm based on clinical symptoms suggestive of myocardial ischemia according to standard practice by experienced invasive cardiologists. Pressure calibration should be confirmed as zero at the proximal segment of the coronary arteries. After calibration, the pressure wire should be advanced to the distal end of the stenosis. Maximal myocardial hyperaemia should be induced by continuous intravenous adenosine infusion via a central or peripheral vein with an infusion rate of 140 μg/kg/min. At the same time, the distal coronary artery pressure at the pressure sensor and the proximal pressure at the coronary ostium will be recorded. A pullback recording should be performed and recorded. The absence of pressure signal drift needs to be confirmed at the distal end of the guiding catheter.

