The DBL-RNN algorithm will be trained using data from 250 patients prospectively enrolled at Beijing Anzhen Hospital. Model weights will be initialized using a calibrated normal distribution to stabilize gradients during the early training phase. To mitigate overfitting, dropout regularization with a rate of 0.5 will be applied to the hidden layers of the network. The loss function will be defined as the squared error (SE) between the CT-FFR values generated by the model and the invasive FFR measurements. Then, the network will be iteratively optimized to minimize this discrepancy, thereby driving the predicted CT-FFR values toward the invasive reference standard. Model optimization will be performed using the Adam optimizer, with a learning rate of 0.0001 and exponential decay rates for the first- and second-moment estimates (β1 = 0.9, β2 = 0.999).

Within the training cohort, internal validation will be performed using a five-fold cross-validation approach. The dataset will be randomly divided into five approximately equal folds. In each iteration, four folds will be used for model training, and the remaining fold will be used for validation. This procedure will be repeated five times, with each fold serving as the validation set once.

Upon completion of training, the model could generate continuous CT-FFR values along the entire length of each coronary artery. All coronary vessels will be labeled according to the 18-segment classification system of the Society of Cardiovascular Computed Tomography (SCCT). During the validation phase, invasive coronary angiography images acquired at the time of invasive FFR measurement will be carefully reviewed to identify the exact anatomical location of the pressure-wire sensor within the three-dimensional coronary model. Then, the corresponding CT-FFR value at this location will be extracted, ensuring precise spatial matching between CT-FFR and invasive FFR measurements.

During the model training phase, CCTA images from the 250 patients enrolled at Beijing Anzhen Hospital will be paired with their corresponding invasive FFR measurements and used as input–output data for model training and parameter optimization.

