### Statistics

All statistical analyses will be performed using Stata version 17.0. The categorical data will be presented as counts with percentages and analyzed using the chi-squared test. Normally distributed continuous variables will be presented as the means ± standard deviations and analyzed using independent sample t-tests. Non-normally distributed continuous variables will be presented as the median (interquartile range) and analyzed using the Mann–Whitney U test. All tests will be two-tailed with p < 0.05 significant.

Baseline demographic, clinical characteristics, and angiographic characteristics, including the percentage of diameter stenosis, will be prospectively collected. These variables will be separately described in the training cohort and the external validation cohort. Comparisons between these two cohorts will be performed to assess comparability, thereby facilitating appropriate interpretation of external validation results. Because FFR primarily performed in intermediate stenosis lesions (30–90% stenosis in vessel diameter), the proportion of intermediate (30–90%) diameter stenosis lesions will be summarized and compared between the two cohorts.

Using invasive FFR as the reference standard, the diagnostic performance of CT-FFR will be evaluated at both the vessel level and the patient level. Only stented segments that undergo invasive FFR measurement will be included in the diagnostic performance analysis. Stented segments without available invasive FFR measurements will not be included in the statistical evaluation due to the absence of a reference standard.

Diagnostic performance of CT-FFR will be evaluated using invasive FFR as the reference standard. A threshold of 0.80 will be used for both CT-FFR and invasive FFR to define functionally significant lesions. Sensitivity, specificity, positive predictive value, negative predictive value, and overall accuracy will be calculated. Receiver operating characteristic (ROC) curves will be constructed, and the area under the curve (AUC) will be calculated to assess diagnostic discrimination.

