At the vessel level, because a single patient may contribute more than one stented vessel, vessel-level observations may not be independent. Therefore, diagnostic performance metrics and their 95% confidence intervals will be estimated using a cluster bootstrap resampling procedure at the patient level (1000 iterations), in which patients will be sampled with replacement, and all corresponding vessel-level observations will be retained in each bootstrap sample.

Agreement between CT-FFR and invasive FFR classifications will be assessed using a cluster-adjusted McNemar test implemented with generalized estimating equations (GEE) with an exchangeable correlation structure to account for within-patient clustering. Continuous CT-FFR and invasive FFR measurements will be assessed using Spearman correlation analysis. Agreement between the two measurements will be further evaluated using Bland–Altman analysis with a linear mixed-effects model, with patient identification number included as a random effect to account for clustering. The mean bias and 95% limits of agreement will be derived from the mixed-effects model.

At the patient level, when multiple stented vessels were present, the vessel with the lowest invasive FFR value will be selected to represent that patient.

The results from the above statistical analyses will be presented in the final study report.

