### Sample size calculation

The sample size calculation was based on previous studies [19] and the following hypothesis: At the patient level, CT-FFR demonstrated an AUC of 0.73(95% CI: 0.55–0.87) for detecting ISR, with a disease prevalence of 76%. A sample size calculation was performed using PASS 2021 (Test for One ROC Curve) with α = 0.05, power = 0.9, and two-tailed testing, yielding a required sample size of 77 patients. We planned to prospectively enroll 81 patients in the external validation cohort, which was expected to provide 90% power to detect an AUC of 0.73.

The training cohort size was defined based on data availability and a predefined training-to-validation ratio of approximately 3:1 to balance model development and independent performance evaluation. Therefore, at least 243 patients were required for model training. Considering clinical practice and data availability, we prospectively planned to enroll 250 patients to meet the sample size requirement, which is comparable to or even larger than the training cohort sizes reported in previous study [20].

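### The patient-level reference rule enters a patient as negative when a stented vessel over 90% or occluded was never measured and every measured stent is above 0.80

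*Protocol article*

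**What the plan says.** Five statements in the protocol article bear on the patient-level label.

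- **Where FFR is done** (Study process): "FFR will be performed in intermediate stenosis (30–90% stenosis in vessel diameter) with a vessel size of at least 2 mm". The Statistics section is slightly looser: "Because FFR primarily performed in intermediate stenosis lesions (30–90% stenosis in vessel diameter".
- **Who is excluded for lack of FFR** (Study design): "Patients without invasive FFR data will be excluded". Nothing in the inclusion and exclusion criteria removes a patient who has FFR in one stent and a tighter, unmeasured stenosis in another.
- **Unmeasured segments** (Statistics): "Stented segments without available invasive FFR measurements will not be included in the statistical evaluation due to the absence of a reference standard".
- **Cut-off** (Statistics): "A threshold of 0.80 will be used for both CT-FFR and invasive FFR to define functionally significant lesions".
- **Patient-level rule** (Statistics): "At the patient level, when multiple stented vessels were present, the vessel with the lowest invasive FFR value will be selected to represent that patient".

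For the index test, the CT-FFR calculation section locates the pressure-wire sensor in the coronary model and says that "the corresponding CT-FFR value at this location will be extracted, ensuring precise spatial matching between CT-FFR and invasive FFR measurements".

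**The concern.** Leaving out an unmeasured vessel is sound at vessel level: without a reference value there is nothing to compare. At patient level the same omission acts differently. Once the unmeasured vessel is gone, the lowest remaining FFR decides the label, so a vessel of unknown status is treated as though it could not change that label. The omission is not random either, because the stated FFR range leaves out the tightest stenoses.

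The patient level matters here because the sample size calculation is set there (AUC 0.73, prevalence 76%). If the rule stands, the patient-level specificity and NPV may include, among the true negatives, patients with an unverified tight restenosis. A reader who takes NPV as the chance that the patient has no functionally significant restenosis would be misled to that extent. The statisticians could not see the problem, because under the CT-FFR calculation section they receive only the paired values, without images or clinical reports.

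**Working it through.** **Step 1. Apply the stated rules to each type of patient with an unmeasured stented vessel over 90% or occluded.**

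| Other stented vessels | In the analysis? | Patient-level label | Sound? |
|---|---|---|---|
| None measured | No, excluded for lack of FFR | None | Not mislabelled (a narrower spectrum only) |
| At least one FFR at or below 0.80 | Yes | Positive | Yes, whatever the unmeasured vessel is |
| All measured FFR above 0.80 | Yes | Negative | No, status unverified |

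Only the third row is a problem. For example, take a 95% stenosis in one stent without FFR, and an FFR of 0.85 in another. The lowest available value is 0.85, which is above 0.80, so the patient is reference-negative.

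**Step 2. What is scored for that patient.** CT-FFR is read at the sensor site of the selected, measured vessel and compared with the FFR at the same site. The unmeasured vessel has no sensor site and no pair, so its CT-FFR does not enter. The 2×2 entry is correct for that vessel. It is not a statement about the patient.

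**Step 3. Reproduce the planned sample size.** The article gives AUC 0.73, prevalence 76% and "α = 0.05, power = 0.9, and two-tailed testing, yielding a required sample size of 77 patients", with 81 planned. It does not state the null AUC; 0.50 is assumed here. With n1 positives and n0 negatives, the Hanley–McNeil variance is

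Var(A) = [A(1−A) + (n1−1)(Q₁−A²) + (n0−1)(Q₂−A²)] / (n1·n0), where Q₁ = A/(2−A) and Q₂ = 2A²/(1+A),

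and power = Φ[(0.73 − 0.50 − 1.96·SE₀)/SE₁], with SE₀ at AUC 0.50 and SE₁ at AUC 0.73.

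- Smallest N for 90% power: 78 (59 positive, 19 negative), against 77 stated. A binormal variance also gives 78.
- N = 77 (59 and 18): power 0.89.
- N = 81 (62 and 19): SE₀ = 0.0762, SE₁ = 0.0601, so (0.23 − 0.1493)/0.0601 = 1.34 and power is 0.91.

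The planned size is reproduced closely and is not in question.

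**Step 4. Weight of one affected patient.** 81 × 0.24 = 19.4, so about 19 reference-negatives. One patient is 1/19 = 5.3% of them.

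**Step 5. Range for the unknown count.** The article gives no frequency, so k affected patients is an assumption. Power uses the Step 3 formula with AUC held at 0.73.

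| k | Share of the 19 negatives | Power if left out (62 vs 19−k) | Prevalence if counted positive | Power if counted positive (62+k vs 19−k) |
|---|---|---|---|---|
| 0 | 0% | 0.91 | 76.5% | 0.91 |
| 1 | 5.3% | 0.90 | 77.8% | 0.90 |
| 2 | 10.5% | 0.88 | 79.0% | 0.89 |
| 3 | 15.8% | 0.87 | 80.2% | 0.87 |
| 4 | 21.1% | 0.85 | 81.5% | 0.85 |

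**The case against.** - **The pair is valid, so specificity is not distorted.** This stands. A reader might infer that a correct CT-FFR alarm in the tight stent is scored as a false positive, so that a specificity of 0.80 would read as 0.80 × (19−k)/19 = 0.76, 0.72 or 0.67 for k = 1, 2 or 3. That would need CT-FFR to be read over all stented vessels of the patient. The article instead matches it to the sensor site of the selected vessel, so these figures are not supported. What remains is a one-vessel-per-patient result presented as patient-level.
- **The subset is narrow.** This also stands. A reader might infer that the reference is wrong for severe restenosis in general. Step 1 shows that it is not: two of the three groups are excluded or correctly positive. The wording in the Statistics section also leaves room for some FFR outside 30–90%, which would shrink the subset further.
- **A stenosis over 90% need not be functionally significant.** The article itself stresses discordance between anatomical and functional severity. The status of such a patient is therefore better called unverified than positive. That supports exclusion as the main analysis, with relabelling only as a sensitivity analysis.
- **It is already disclosed.** This stands only in part. The Limitation section admits referral and verification bias, but as a question of how far results carry over to broader post-stent populations. It does not mention the label given to patients inside the analysed cohort.

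**Conclusion.** The point holds in a limited form. The rules as written enter a patient as reference-negative when a stented vessel over 90% or occluded has no FFR and every measured stent is above 0.80. No statement in the article gives that vessel a status or removes the patient from the patient-level analysis. The consequence lies in what patient-level specificity and NPV mean, since such a patient can be counted as a true negative; the matched comparison in the selected vessel is not in error.

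The size is unknown. Each affected patient is about 5% of roughly 19 negatives, assuming that the planned 76% prevalence is met in 81 patients. The number of such patients is not given and could be zero. The sample size is not at fault. This is a worthwhile, inexpensive improvement to a stated rule, not a defect that undermines the study.

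**What to change.** 1. Keep the vessel-level rule unchanged.
2. Have the third-party investigator who matches the two datasets pass on one flag per patient: any stented vessel over 90% or occluded without FFR, taken from the percent diameter stenosis already being collected. The statisticians stay blinded to images and reports.
3. Leave flagged patients with no FFR at or below 0.80 out of the main patient-level analysis. Flagged patients with any FFR at or below 0.80 stay positive.
4. Add a sensitivity analysis that counts the omitted patients as reference-positive, and state beforehand which CT-FFR value stands for them, since the unmeasured vessel has no sensor site.
5. Report how many there are. Patients whose only unmeasured stents are at or below 90% stay under the present rule, with their number reported, so that nobody is left without a status.

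The cost is a few sentences, one data flag and the loss of a few patient-level negatives: power of about 0.90 to 0.85 for one to four patients, assuming a null AUC of 0.50. No change to the clinical indication for FFR is implied.

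### At patient level, invasive FFR decides which vessel's CT-FFR is scored, so specificity can only be overstated and sensitivity only understated, probably by a few points

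*Protocol article*

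**What the plan says.** The Statistics section announces two levels of analysis: "the diagnostic performance of CT-FFR will be evaluated at both the vessel level and the patient level". The cut-off is common to both tests: "A threshold of 0.80 will be used for both CT-FFR and invasive FFR to define functionally significant lesions". Eligible vessels are limited by the reference test: "Only stented segments that undergo invasive FFR measurement will be included in the diagnostic performance analysis".

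At vessel level the plan keeps all measured vessels and allows for clustering, "because a single patient may contribute more than one stented vessel, vessel-level observations may not be independent". At patient level it reduces each multivessel patient to one vessel: "the vessel with the lowest invasive FFR value will be selected to represent that patient".

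The CT-FFR calculation section fixes where CT-FFR is read. The wire sensor is located on the angiogram, and "the corresponding CT-FFR value at this location will be extracted, ensuring precise spatial matching between CT-FFR and invasive FFR measurements". Nowhere does the article define a patient-level CT-FFR result from CT-FFR alone.

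The Sample size calculation section sizes the validation cohort at patient level, on AUC: "At the patient level, CT-FFR demonstrated an AUC of 0.73(95% CI: 0.55–0.87) for detecting ISR". The Limitation section discusses referral, verification and image-quality selection, but not this rule.

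**The concern.** Taking the lowest invasive FFR is a sound way to set a patient's reference status. The difficulty is that the same choice also settles which CT-FFR value enters the patient-level table. Two kinds of result then drop out of that table:

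- In a patient whose measured vessels all have FFR above 0.80, a CT-FFR of 0.80 or less in a vessel that was not selected. This false positive is not counted.
- In a patient with at least one FFR of 0.80 or less, a positive CT-FFR found only in a vessel that was not selected. The patient is scored as a miss although CT-FFR would have flagged the patient.

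The Discussion presents the model as giving a diagnosis without an invasive procedure. Before the invasive test nobody knows which vessel has the lowest FFR, so a patient-level figure built on that knowledge describes a reading that cannot be made in use.

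**Working it through.** **1. The plan's own figure.** Inputs from the Sample size calculation section: AUC 0.73, prevalence 76%, two-sided alpha 0.05, power 0.90, required N 77, planned N 81. The null AUC is not stated; 0.50 is assumed. The Hanley-McNeil variance is

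Var(A) = [A(1−A) + (n₁−1)(P₁−A²) + (n₂−1)(P₂−A²)] / (n₁n₂), with P₁ = A/(2−A) and P₂ = 2A²/(1+A).

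With n₁ = 59 positive and n₂ = 19 negative (N = 78):

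- SE at A = 0.50: √(6.583/1121) = 0.0766
- SE at A = 0.73: √(4.124/1121) = 0.0607
- Power = Φ[(0.23 − 1.96 × 0.0766)/0.0607] ≈ 0.906

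The smallest N reaching 90% power is 78, against 77 stated; power at 81 is 0.911. The sample size reproduces and is not in dispute.

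**2. Direction, by logic.** Both rules use the same reference: positive if the lowest invasive FFR is ≤0.80. Let S mean that the selected vessel has CT-FFR ≤0.80, and M that the lowest CT-FFR over the measured vessels is ≤0.80. S implies M, but M does not imply S. Hence:

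- specificity (plan) − specificity (lowest CT-FFR) = P(M and not S | reference negative) ≥ 0
- sensitivity (plan) − sensitivity (lowest CT-FFR) = −P(M and not S | reference positive) ≤ 0

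The only patients affected are those in *M and not S*: selected vessel above 0.80, another measured vessel at or below 0.80. A patient with one measured vessel is never affected.

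**3. Simple illustration.** Assume two truly negative vessels, per-vessel specificity 0.80 and independent errors. The plan gives 0.80; the lowest-CT-FFR rule gives 0.80² = 0.64. If a share f of reference-negative patients has two vessels, the latter becomes (1−f) × 0.80 + f × 0.64: 0.784 at 10%, 0.752 at 30%, 0.72 at 50%. This overstates the likely gap, because the vessel not selected has the higher FFR and so tends to lie further from the cut-off.

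**4. Simulation.** Assumptions, none of which the document supplies: up to two measured vessels, FFR SD 0.10, CT-FFR error SD 0.07 or 0.10 and independent between vessels, between-vessel FFR correlation 0 or 0.3, mean set to give about 76% prevalence, 1,000,000 patients per scenario. Plan minus lowest-CT-FFR rule, in percentage points:

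| Two-vessel share | Specificity | Sensitivity |
|---|---|---|
| 0% | 0 | 0 |
| 10% | +0.3 to +0.5 | −0.4 to −0.8 |
| 30% | +1.1 to +1.8 | −1.5 to −2.6 |
| 50% | +2.3 to +3.5 | −2.5 to −4.3 |
| 100% | +6.9 to +10.5 | −4.8 to −8.2 |

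AUC differs by about 0.01 or less. Simulated AUCs at shares of 10% to 50% were about 0.84 to 0.91, above the planning value of 0.73. The gaps widen as the CT-FFR error SD goes from 0.07 to 0.10, so a test nearer the planning AUC could show larger ones. Errors correlated between vessels of one scan would shrink them.

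**5. Against sampling error.** 0.76 × 81 ≈ 62 reference-positive patients, leaving about 19 negative.

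- SE of a specificity of 0.80: √(0.80 × 0.20/19) = 0.092
- SE of a sensitivity of 0.82: √(0.82 × 0.18/62) = 0.049
- Expected reclassified patients at a 30% share: 19 × 0.011 to 0.018 = 0.2 to 0.3 negatives, and 62 × 0.015 to 0.026 = 0.9 to 1.6 positives
- One reclassified negative moves specificity by 1/19 ≈ 5 points

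**The case against.** The other side has several good arguments.

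- **Size.** The likely shift is well inside sampling error, and the multivessel share could be small. This stands and limits the severity. It does not remove the point: the direction is fixed in advance and is built into the rule.
- **Vessel level.** Every measured vessel is kept there, with patient-level cluster bootstrap, so the false alarms and hits are reported somewhere. This stands; they are missing only from the patient-level summary.
- **A different target.** CT-FFR performance in the FFR-worst vessel is a coherent quantity, and the rule is valid for it. This stands too, but the quantity should carry that name and not be presented as patient-level accuracy.
- **Wrong-vessel credit.** Scoring by lowest CT-FFR counts a patient as a true positive when the ischaemic vessel was missed and another was flagged. That is a real, small cost. Localisation is what the vessel-level analysis measures.
- **The fix also depends on FFR.** CT-FFR values would still come only from vessels with invasive FFR, read at the wire position. True: the fix stops FFR choosing among the measured vessels and nothing more.
- **Wording.** The rule does not say outright that the same vessel's CT-FFR is scored, and an analysis plan not shown may say more. Given the wire-position matching, that is nonetheless the natural reading of a rule the article does state.

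A reader might also infer that blinding fails. It does not: CT-FFR is computed without access to FFR and paired afterwards by a third party, so no CT-FFR value is altered, only chosen.

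**Conclusion.** The point holds at moderate severity. The patient-level rule lets the reference standard pick the index-test value. Relative to a CT-FFR reading possible without invasive FFR, it can only raise specificity and only lower sensitivity. With an assumed 10% to 50% of patients having two measured stented vessels, and the simulation assumptions above, the whole-cohort shift is roughly 0.3 to 3.5 points in specificity and 0.4 to 4.3 points in sensitivity, with AUC moving by about 0.01 or less. It is zero if nobody has more than one measured vessel.

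Three stronger readings are tempting but not supported. The fall from 0.80 to 0.64 applies only to patients with two negative vessels and independent errors; it is not a forecast for the cohort. Not every multivessel patient is misscored, only those with the discordant pattern described. And although the cohort is sized at patient level, it is sized on AUC, which barely moves, so neither the 77 nor the 81 is called into question.

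**What to change.** Reword the patient-level rule in the Statistics section as follows:

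- Patient-level reference: the lowest invasive FFR over the measured stented vessels, positive if ≤0.80.
- Patient-level index test: the lowest CT-FFR over those same vessels, positive if ≤0.80, chosen without reference to FFR.
- Use these two for patient-level sensitivity, specificity, predictive values, accuracy and AUC.
- Keep the current rule as a sensitivity analysis, labelled as CT-FFR performance in the FFR-worst vessel, and refer readers to the vessel-level results for localisation.
- Report how many validation patients have more than one measured stented vessel, so that the effect of the choice is visible.

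The cost is a short text change with no new data, no extra patients and no change to the sample size. Recruitment is described as ongoing, so the definition can still be fixed before results are known; a later change would look post hoc.
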